| Principal criteria                                                                                                                                                                                                                                                                                                                                                                                                                                                                                                                                                                                                                                                                                                                                                                                                                                                                                                                                                  |
| 
Clinical remission at month-12 (KDIGO definition):
 
 
- complete: UPCR <0.3 g/g in spot morning urine samples and Normal serum albumin and eGFR > 60 ml/min/1.73 m^2
 
- partial: UPCR < 3.5 g/g with a decrease greater than 50% from baseline and improvement or normalization of the serum albumin concentration and increase of serum creatinine lower than 20%
 
                                                                                                                                                                                                                                                                                                                                                                                                                                                                                                                        |
| Methodology and biostatistics                                                                                                                                                                                                                                                                                                                                                                                                                                                                                                                                                                                                                                                                                                                                                                                                                                                                                                                                       |
| 
Biometry department of the Délégation à la Recherche Clinique et à l'Innovation of Nice University Hospital
                                                                                                                                                                                                                                                                                                                                                                                                                                                                                                                                                                                                                                                                                                                                                                                                                                                  |

***Abbreviations used in this document***

MN : Membranous Nephropathy

iMN : idiopathic Membranous Nephropathy

NEP : Neutral Endopeptidase

PLA2R1 : m-type phospholipase A2 receptor

THSD7A : Thrombospondin type-1 domain containing 7A

KDIGO : Kidney Disease Improving Global Outcome

ELISA : Enzyme Linked Immunosorbent Assay

IFA : Immunofluorescence Assay

CD20 : Cluster Differentiation 20

NIAT : Non immunosuppressive antiproteinuric treatment

CTLD : C-type lectin domain

CysR : Cysteine-rich domain

eGFR : estimate glomerular filtration rate

CKD-EPI: Chronic Kidney Disease-EPIdemiology collaboration

UPCR : Urinary protein/creatinine ratio

UACR : Urinary albumin/creatinine ratio

TReg : Lymphocyte T regulator

HBC : Hepatitis B virus

HCV : Hepatitis C virus

eCRF : electronic case report file

IL-35 : Interleukin 35

LOCF : Last Observation carried forward

Ab : antibodies

GEMRITUX protocol: 6 months of symptomatic antihypertensive and antiproteinuric therapy, and if the nephrotic syndrome persists at month-6 (UPCR remains > 3.5 g/g and albuminemia < 30 g/l), treatment with two 375 mg/m^2 infusions at 1-week interval.

## **1. General description and scientific rationale**

### **1. 1 Current context**

Membranous nephropathy (MN) is a rare disease with an incidence of 1,3 cases/ 100 000 people/year in France (1) but it can be severe: the risk of end stage kidney disease involves 1 out of 5 male and 1 out of 12 females, 15% of patients with MN were at risk to reach end stage kidney disease after at least 10 years of disease evolution. It is the first cause of nephrotic syndrome in adults (2, 3).

MN is defined by subepithelial immune deposits containing IgG with alteration of the membrane structure. MN can be idiopathic (or primary) without any identified cause (70-80% of cases), or secondary to clinical disorders such as hepatitis B, systematic lupus erythematosus, cancer and drug side effect (4, 5). Idiopathic MN (iMN) is an autoimmune disease directed against a podocyte antigen, such as neutral endopeptidase (NEP) in the neonate, M-type phospholipase A2 receptor (PLA2R1) and thrombospondin type-1 domain-containing 7A (THSD7A) in 70-80% and <5% adult patients respectively (6-8). The pathogenic role of PLA2R1-antibodies (Ab) is not yet proven, but antibody titers usually rise during clinically active phases and decrease before normalization of proteinuria (9, 10). Spontaneous remission occurs in about one third of patients, and kidney failure in another third (11, 12). High titers of PLA2R1-Ab at presentation and their persistence predict poor clinical outcome (13, 14). Therefore, reducing PLA2R1-Ab levels has become an important goal of therapy.

The treatment of iMN is controversial. Kidney Disease Improving Global Outcomes (KDIGO) guidelines recommend a supportive symptomatic treatment with blockers of the renin-angiotensin system and diuretics in all patients with iMN, and immunosuppressive therapy only in the case of renal function deterioration or persistent nephrotic syndrome. Therefore, immunosuppressive treatments are often started only after significant and potentially irreversible complications. On the other hand, an unnecessarily early start of immunosuppression can be futile in patients who develop remission with symptomatic treatments. Therefore, there is a need for better predictors of renal outcome in iMN.

KDIGO guidelines recommend an initial immunosuppressive therapy with a 6-month course of alternating monthly cycles of oral and intravenous corticosteroids and oral alkylating agent (cyclophosphamide rather than chlorambucil for initial therapy) (recommendation grade 1B and 2B). Cyclosporine or tacrolimus can be used as alternative regimens for the initial therapy

(recommendation grade 1C). All these immunosuppressive treatments are associated with side effects (15).

The anti-CD20 antibody (rituximab) has been increasingly used off-label in iMN, like in other B-cell dependent diseases with a low rate of side effects. Rituximab can trigger B-cell death and induce PLA2R1-Ab depletion and clinical remission in 60-80% of patients with iMN in several non-randomized study (9, 16, 17). Its long-term efficacy was established in a recent randomized controlled study (GEMRITUX). Seventy-five iMN patients (PLA2R1-Ab+ n=58, and PLA2R1-Ab- n=17 using IFA) with nephrotic syndrome after 6-months therapy with non-immunosuppressive antiproteinuric treatment (NIAT) were randomly allocated to 375mg/m^2 intravenous rituximab plus NIAT on days 1 and 8 (n=37) or NIAT alone (n=38). After 6 months, remission rate (35.1% in rituximab group vs 21.1% in NIAT alone group) was not different between the 2 groups (p=0.21), while remission rate after a median time of 17 months during observational phase were higher in the rituximab group (64.9% vs 34.2% respectively p<0.01) (18). The negative results of this study at 6 months raise the question of the **selection of patients that received immunosuppressive therapy** and of the **dose of rituximab used**.

## 1.2 Epitope Spreading as prognosis biomarker

Our first objective is to better select patients who will benefit from immunosuppressive treatment. Although the identification of PLA2R1-Ab has been paradigm shifting in the diagnosis and management of patients, there are outliers who call for additional biomarkers. Indeed, antibodies may persist during apparent clinical remission and conversely a drop in antibody titer may not be associated with a clinical remission (14, 19, 20).

PLA2R1 is a 180-kDa membrane receptor with a large extracellular region comprising 10 distinct globular domains including a cysteine-rich domain (CysR), a fibronectin type II domain (FNII), and 8 distinct C-type lectin domains (CTLD1-8) (21). Each domain is separated by a small linker sequence of about 10 amino acids. An immunodominant epitope was first identified in a region spanning the CysR-FNII-CTLD1 domains (22), which was further restricted to the CysR domain alone (23). In a first study, we identified reactive epitopes in the CysR, CTLD1 and CTLD7 domains, and that all samples reacted with CysR domain confirming that CysR was the immunodominant epitope. We further showed that patients with anti-CysR-restricted activity were younger, had lower proteinuria, and exhibited a higher rate of spontaneous remission and lower rates of renal failure progression (24). Conversely, high PLA2R1-Ab activity and epitope spreading beyond the CysR epitope were

independent risk factors of poor renal prognosis in a collection of 69 sera from five French nephrology centers.

In a second prospective trial we analyzed the predictive value of epitope-specific PLA2R1-Ab titer and epitope spreading at diagnosis in the 58 PLA2R1-Ab positive patients from GEMRITUX randomly allocated to rituximab plus NIAT (n=29) or NIAT (n=29). In adjusted analysis, epitope spreading at baseline was associated with a decreased remission rate at month 6 (OR, 0.16; 95% CI, 0.035 to 0.72;  $p=0.0171$ ) and last follow-up (median, 23 months; OR, 0.14; 95% CI, 0.03 to 0.64;  $p=0.0107$ ), independently from age, gender, baseline PLA2R1-Ab level and treatment group (Seitz-Polski et al. JASN Accepted august 2017).

Our findings led us to hypothesize that PLA2R1-Ab may be initially raised against the N-terminal CysR domain with pauci-symptomatic iMN disease: patients in the CysR group are younger than in the others groups, suggesting that these patients are probably at the beginning of the disease and should entered in spontaneous remission. Some patients could be asymptomatic at this stage. A second immune challenge (allergy, infection...) might then induce intramolecular spreading in PLA2R1 toward the C-terminal end (CTLD1 or CTLD7) leading to more active disease.

**Figure 1: MN sera exhibit 1, 2 or 3 distinct antibodies targeting different PLA2R1 domains Working hypothesis of natural history: 1. CysR as the first immunodominant epitope. 2. Epitope spreading towards CTLD1 and CTLD7**

[figure not shown]

***We conclude that epitope spreading at baseline should be considered for early therapeutic intervention in patients with iMN.***

**Figure 2: Monitoring of epitope spreading as a clinical biomarker**[figure not shown]

### 1.3 Rituximab protocol

Our second objective is to adapt the dose of rituximab to the immunological activity of the disease. There are still uncertainties regarding the protocol of rituximab that should be used in heavily nephrotic patients (25). Cravedi et al. proposed to titrate rituximab to CD20 cell counts (26). Fervenza et al. showed that four doses of rituximab resulted in more effective B-cell depletion, but proteinuria reduction was similar in patients who received 2 doses of 1g at one-week interval (27). Pharmacokinetic studies have demonstrated a large inter-individual variability, related to either disease or genetic factors, which could explain differences in clinical response (28-31). Residual rituximab serum levels were detected in some patients up to 6 to 9 months after the first infusion due to recycling from endothelial cells via FcRn receptor. In patients with MN, rituximab half-life was calculated as 11.5 days, compared to 18.0 days in patients with rheumatoid arthritis (27). We detected rituximab in urine from one patient with iMN 15 days after his first infusion.

We compared two regimens of rituximab in 2 cohorts of anti-PLA2R1 positive MN patients with similar clinical characteristics: 19 patients from Nice treated with two 1-g infusions at 2-week interval, and 27 patients from the GEMRITUX trial treated with two 375 mg/m^2 infusions at 1-week interval. We measured serum rituximab levels at months 3 and 6. Remissions occurred at month 6 in 13 (68.4 %) Nice patients and 8 (29.6%) GEMRITUX patients ( $p=0.02$ , 3 complete remissions vs none), and during follow-up in 16 (84.2%) Nice patients and 18 (66.6%) GEMRITUX patients (NS). Median time to remission was 3 and 9 months, respectively ( $p=0.02$ ). The higher remission rate at month 6 was associated with higher serum rituximab levels at month 3 ( $p=0.004$ ) and lower CD19 count at month 3 and month 6 ( $p=0.002$  and  $0.0004$ , respectively). In both treatment groups,

remission was associated with higher rituximab level ( $p=0.006$ ), lower CD19 count ( $p=0.01$ ) and PLA2R1 antibody titer ( $p=0.007$ ) at month 3 (Seitz-Polski et al. in preparation). In conclusion, early clinical remission is dependent on rituximab protocol and correlated with serum rituximab level and CD19 count at month 3.

[figure not shown]

**Figure 4: Flowchart of the 19 patients from Nice and the 27 patients from GEMRITUX cohort, all with PLA2R1-Ab: outcome at month 6 after rituximab infusion**

[figure not shown]

**Figure 5: Residual serum rituximab concentration at month 3.** Comparison of Nice (n=19, 2 infusions, 1g, 2-week interval) and GEMRITUX (n=27, 2 infusions, 375 mg/m^2, one-week interval) cohorts. Note the variability of residual rituximab concentrations and lower concentrations in the GEMRITUX patients.

In GEMRITUX cohort, remission rate at month 6 under rituximab was higher in patients with anti-PLA2R1 activity restricted to CysR than in patients with epitope spreading (70.0% vs 24.0% n=29  $p=0.04$ ).

***We concluded that:***

- ***early remission rate depends on rituximab dosing,***
- ***low dose of rituximab could be enough for patients with anti-PLA2R1 activity restricted to CysR,***
- ***high dose of rituximab may be required for patients with epitope spreading.***

We will compare two therapeutic strategies in PLA2R1-related iMN patients to induce clinical remission of the nephrotic syndrome at month 12:

1. The strategy validated in the GEMRITUX protocol: 6 months of symptomatic antihypertensive and antiproteinuric therapy, and if the nephrotic syndrome persists at month 6 (UPCR remains > 3.5 g/g and albuminemia < 30 g/l), two 375 mg/m^2 infusions at 1-week interval.

2. A personalized strategy driven by the PLA2R1-Ab epitope profile at month 0 and month 6:

- Patients with restricted anti-CysR activity at month 0: these patients have a spontaneous remission rate under NIAT from 43% to 50% at month-6. We propose a symptomatic antihypertensive and antiproteinuric treatment for 6 months;
- Patients with restricted anti-CysR activity and persisting active disease at month 6 after symptomatic treatment (UPCR remains > 3.5 g/g and albuminemia < 30 g/l): in GEMRITUX, these patients have a high rate of remission with low dose of rituximab (about 70%). We propose two 375 mg/m^2 rituximab infusions at 1-week interval;
- Patients with anti-CTLD1/7 activity at month 0 or month 6 with persisting active disease after symptomatic treatment (UPCR remains > 3.5 g/g and albuminemia < 30 g/l): these patients have a very low rate of spontaneous remission under NIAT (from 0.05% to 17%) or under low dose of rituximab: in GEMRITUX 24% of remission at 6-month vs 64% with high dose of rituximab p=0.04. We propose to treat these patients with high dose of rituximab (two 1g rituximab infusions at 2-week interval at month 0 and/or month 6).

Ruggenti et al. demonstrated on a cohort of 81 consecutive iMN patients with PLA2R1-Ab that PLA2R1-Ab depletion 6 months post-rituximab strongly predicted remission (HR, 7.90; 95% CI, 2.54 to 24.60; P<0.001) (32). We will reevaluate the serologic status of all patients at month-6 and retreat according to the same protocol.

Two studies showed that a significant increase in TReg cells from month 6 after rituximab infusion is associated with clinical response (33, 34). This increase is associated with IL-35 increase and PLA2R1-Ab decrease (33). IL-35 is an inhibitory cytokine that contribute to regulatory T-cell function. These results must be confirmed in large cohort to understand mechanisms of rituximab resistance and proposed new strategies (35). We propose to confirm these results in an ancillary study.

#### 1.4 MN recurrences

The rate of iMN recurrences after rituximab infusion is about 30% (32). MN recurrences are associated with rise in PLA2R1-Ab titers (9, 32). In our cohorts (Nice cohort + GEMRITUX), 7 patients out of the 34 who reached remission relapsed. MN recurrences after rituximab were associated with the appearance of anti-rituximab antibodies at month 6 ( $p=0.02$ ) and higher PLA2R1-Ab titer at month-3 and month-6 ( $p=0.04$  and  $0.03$  respectively). In competition assays, anti-rituximab antibodies could block in vitro complement and cell dependent rituximab cytotoxicity on B-cells. Inhibition of rituximab activity could favor the persistence of pathogenic memory B-cells and induce disease relapse, with an early reconstitution of the B-cell compartment (36). We will monitor serum rituximab levels at month 3 and month-6, anti-rituximab antibodies at month-3 and month-6 as well as at inclusion for relapsing patients, and B-cell compartments (transitional, mature/naïve, memory) at Month 0, Month 3, Month 6, Month 12 and Month 18 after rituximab infusion to correlate the appearance of anti-rituximab antibodies and the re-emergence of the memory B-cell with MN recurrences in an ancillary study.

## 2. Study objectives

### 2.1 Primary objective

Our main objective is to compare the efficacy of a **personalized treatment** of nephrotic iMN driven by anti-PLA2R1 antibody epitope profile at month 0 and month 6 to induce clinical remission (partial or complete) of the nephrotic syndrome at month 12:

- Restricted anti-CysR activity at month 0: 6-month symptomatic treatment
- Restricted anti-CysR activity at month 6 after symptomatic treatment and if the nephrotic syndrome persists at month-6 (UPCR remains  $> 3.5$  g/g and albuminemia  $< 30$  g/l): two 375 mg/m^2 rituximab infusions at 1-week interval

- Anti-CTLD1/7 activity at month 0 or month 6: two 1g rituximab infusions at 2-week interval at month 0 and/or month 6

with the GEMRITUX protocol: 6 months of symptomatic antihypertensive and antiproteinuric therapy, and if the nephrotic syndrome persists at month-6 (UPCR remains > 3.5 g/g and albuminemia < 30 g/l), two 375 mg/m^2 infusions at 1-week interval. For patients who will develop anti-rituximab antibodies, treatment with human anti-CD20 is widely recommended.

## 2.2 Secondary Objectives

The following objectives are to compare between a personalized treatment of iMN driven by anti-PLA2R1 antibody epitope profiles and the GEMRITUX therapeutic protocol:

1. Complete clinical remissions at M6, M9, M12, M18, M24
2. Partial clinical remission at M6, M9, M12, M18, M24
3. Immunological remissions at M6, M9, M12, M18, M24
4. Proteinuria and albuminuria at M6, M9, M12, M18, M24
5. Changes in proteinuria and albuminuria from baseline at M6, M9, M12, M18, M24
6. Serum creatinine and estimated glomerular filtration rate (eGFR) at M6, M9, M12, M18
7. Changes in serum creatinine and eGFR from baseline at M6, M9, M12 and M18
8. PLA2R1-Ab titers at M6, M9, M12, M18 and M24
9. Recording all AEs/SAEs during study follow-up, 24 months

The following objectives aim to study risk factors for remission or relapse:

10. To determine risk factors for remission (immunological and clinical, partial or complete) at M12 in patients pooled from the two arms
11. To determine risk factors for relapse (between M12 and M24) in patient responders at M12, pooled from the two arms

## 3. Evaluation criteria

### Principal evaluation criteria:

Clinical remission will be defined as a composite criterion combining (KDIGO definitions):

- Complete clinical remission: urinary protein/creatinine ratio (UPCR)<0.3 g/g in spot morning urine samples and Normal serum albumin and eGFR > 60 ml/min/1.73 m^2

- Partial clinical remission: UPCR < 3.5 g/g with a decrease greater than 50% from baseline and improvement or normalization of the serum albumin concentration and increase of serum creatinine lower than 20%

Secondary evaluation criteria:

1. Complete clinical remission as defined above
2. Partial clinical remission as defined above
3. Immunological remission: full PLA2R1 depletion measured by ELISA (titer<14RU/ml)
4. Proteinuria and albuminuria are measured on urine sample (proteinuria-to-creatinine ratio or albuminuria-to-creatinine ratio g/g) or collected during one day (g per day)
5. Change in proteinuria are measured in percentage change in proteinuria from baseline to M6, M9, M12, M18, M24
6. Serum creatinine is measured in blood sample in  $\mu\text{mol/l}$  and eGFR using the CKD-EPI formula.
7. Change in serum creatinine and eGFR are measured in percentage change from baseline to M6, M9, M12, M18, M24
8. PLA2R1-Ab titer are measured by ELISA in RU/ml
9. Severe infections are defined as infections that led to hospitalization during study follow-up
10. Remission will be defined as already stated. Patients from both groups will be analysed jointly. The following risk factors will be studied in this analysis:
  - Lymphocyte counts: B cells (CD19, transitional, mature and memory) and T cells (CD3, CD4, CD8 and TReg) measured in blood sample at J0, M3, M6, post-rituximab infusion
  - Serum level of cytokines (pg/ml) measured in blood sample at J0, and after first remission (or M24 if no remission)
  - Residual serum rituximab levels ( $\mu\text{g/ml}$ ) measured in blood sample at M3 post-rituximab infusion using ELISA
  - Neutralizing anti-rituximab antibodies (ng/ml) measured in blood sample at M3 and M6 post-rituximab infusion
11. Responders are patients entered in partial or complete remission at M12. Relapse is defined by an increased proteinuria > 3.5 g/g after remission at M12. Patients from both groups will be analysed jointly. The risk factors studied will be the same as above measured at J0, M3, M6, M9 and M12 post-rituximab infusion.

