## **6. Selection and exclusion criteria for study participants**

### **6.1 Inclusion criteria**

- Age 18 years or more
- Anti-PLA2R1 activity detected by ELISA or Euroimmune IFA
- Nephrotic syndrome defined by proteinuria > 3.5 g/24h (or UPCR > 3.5 g/g) and serum albumin < 30 g/L at diagnosis
- eGFR (CKD-EPI) > 30 ml/min/1.73 m^2 at diagnosis
- Symptomatic treatment according to KDIGO guidelines: maximal tolerated dose of NIAT (angiotensin-converting enzyme inhibitor and/or angiotensin 2 receptor blockers, diuretics and statins)
- Medical insurance
- Signed informed consent
- Having understood and accepted the need for long-term medical follow-up
- Woman of child-bearing age must be using an effective method of contraception

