## 6.2 Exclusion criteria

- Secondary MN: MN related to cancer, infectious, systemic lupus erythematosus, drug
- Anti-PLA2R1 antibodies not confirmed by central analysis (in this case the patient will be replaced)
- Pregnancy or breastfeeding
- Immunosuppressive treatment in the 6 last months
- Presence of anti-rituximab antibodies for relapsed patients
- Cancer under treatment
- Patient with complicated nephrotic syndrome that would require early immunosuppressive treatment (thrombosis, acute renal failure...)
- Patients with active, severe infections or active hepatitis B
- Hypersensitivity to the active substance or to murine proteins, or to any of the other excipients
- Patients in a severely immunocompromised state
- Severe heart failure (New York Heart Association Class IV) or severe, uncontrolled cardiac disease
- Patients unable to give an informed consent

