### **8.2 Patient selection for this study**

Patients with clinical diagnosis of MN will be tested for the presence of PLA2R1-Ab according to local practices. The selection of the patients fulfilling the inclusion criteria will not delay the start of the symptomatic treatment according to KDIGO guidelines. If the patient meets the criteria for recruitment to the study, they will be informed of the study by the referring nephrologist. Full information will be supplied orally, together with written information.

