### **12.3.2 Analysis of the main secondary objective:**

The secondary objectives consist in comparing several parameters between both treatment groups (GEMRITUX versus Personalized treatment) at different study timepoints according to each specific objective. The secondary assessment criteria can be grouped into two categories:

- Objectives 1, 2 and 3: binary criteria (remission clinical or immunological), compared at different timepoints between the two groups. Comparisons will be performed using a Chi-square test or Fisher's exact test in case of small sample.
- Objectives 4, 6 and 8: quantitative criteria compared at different timepoints between the two groups. Comparisons will be performed using a student t-test (or mann-whitney rank sum test in case of non-parametric variables).
- Objectives 5, 7: Quantitative criteria evolution (changes from baseline), defined as the difference between the  $M_x$  and  $D_0$  values,  $\Delta\text{variable} = \text{Variable } M_x - \text{Variable } D_0$ . Analyses will use an analysis of covariance which takes into account the initial values as a covariate. The dependent variable will be the  $\Delta\text{variable}$  and the variable of interest the treatment group.
- Objective 9: Severe infections will be described by type and their frequencies, absolute and relative, presented. The rate of patients presenting with at least one severe infection during follow-up will be compared between the two groups using a Chi-square test or Fisher's exact test in case of small sample.

Further multivariate analyses will be eventually discussed in case of imbalanced potential confounding factors between the groups.

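### Immunological remission is an ELISA titre below 14 RU/ml with no condition at M0, and the protocol does not rule out patients who are already below that level at entry

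*Protocol*

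**What the plan says.** **Endpoint.** Protocol section 3, secondary criterion 3, reads "Immunological remission: full PLA2R1 depletion measured by ELISA (titer<14RU/ml"). Criterion 8 in the same section adds "PLA2R1-Ab titer are measured by ELISA in RU/ml". Neither mentions the M0 titre. Partial clinical remission, defined just above, does require a change from baseline.

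**Entry.** Section 6.1 asks for "Anti-PLA2R1 activity detected by ELISA or Euroimmune IFA", with no minimum titre. Section 8.2 leaves the selection test to the sites: "Patients with clinical diagnosis of MN will be tested for the presence of PLA2R1-Ab according to local practices".

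**Central check.** Section 6.2 lists as an exclusion "Anti-PLA2R1 antibodies not confirmed by central analysis (in this case the patient will be replaced"). It names no assay and no cut-off. Section 8.5 sends M0 blood from both arms to the central laboratory for PLA2R1 antibodies and the epitope profile.

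**Analysis.** Section 2.2 lists "Immunological remissions at M6, M9, M12, M18, M24" as objective 3. Section 12.3.2 treats it as a plain comparison of rates: "Objectives 1, 2 and 3: binary criteria (remission clinical or immunological), compared at different timepoints between the two groups". Section 12.1 sets intention to treat as the main population, with no subset for this criterion. Objective 10 looks for risk factors for remission at M12, immunological remission included, with the arms pooled.

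**The concern.** The name of the endpoint implies a fall in antibody, but the rule tests only a level. The tests that admit a patient need not be the test that defines the endpoint, and nothing in the text links eligibility to 14 RU/ml. A patient who is positive at a site by IFA, and confirmed centrally by some method other than ELISA at 14 RU/ml or above, could start the trial below the endpoint threshold. If the titre stayed there, every later visit would record a full depletion that never took place.

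Three things are at stake:

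- Both arms' immunological remission rates would be too high.
- The difference between arms in objective 3 would be diluted.
- Objective 10 would class as remitters some patients who had nothing to remit from.

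M6 is the most sensitive visit. The GEMRITUX arm has had no rituximab by then, so patients who were low from the start could form a noticeable part of its few remissions.

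**Working it through.** **1. Can a patient below 14 RU/ml at M0 be in the trial?**

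| Step | Protocol section | Requires at least 14 RU/ml by ELISA? |
|---|---|---|
| Local test | 6.1, 8.2 | No: ELISA or IFA, no minimum |
| Central confirmation | 6.2 | Not stated: no assay, no cut-off |
| Definition of the endpoint | 3, criterion 3 | No condition at M0 |
| Analysis of objective 3 | 12.1, 12.3.2 | No restriction to patients above the threshold at M0 |

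Only central confirmation could close the gap. It does so if it means ELISA at 14 RU/ml or above, and otherwise not. The text does not settle which.

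**2. When would such a patient be counted?** M0 is not an analysis time point. The patient counts only if the titre is below 14 RU/ml at M6, M9, M12, M18 or M24.

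**3. Size, as an illustration.** The protocol gives no expected immunological remission rate and no share below the threshold at M0, so there is no figure of its own to reproduce. Assumptions:

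- A share p of each arm is below 14 RU/ml at M0 and stays below it.
- The remaining patients have rates of 30% and 60%.
- There are 32 patients per arm (64 in total, section 7.2, randomised 1:1) and a two-sided test at 5%.

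Observed rate = p + (1-p) × rate among patients at or above 14 RU/ml at M0.

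Observed difference = (1-p) × difference among those patients. This factor does not depend on the two rates chosen.

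Power = Φ{[d − 1.96√(2m(1−m)/n)] / √[(a(1−a)+b(1−b))/n]}, where a and b are the two rates, m is their mean, d = b − a and n is the number per arm. For the restricted analysis n = 32(1-p), with rates of 30% and 60%.

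| p | Patients of 64 | Observed rates | Difference (points) | Power, all patients | Power, restricted to ≥14 at M0 |
|---|---|---|---|---|---|
| 0% | 0 | 30.0% vs 60.0% | 30.0 | 68.2% | 68.2% |
| 5% | 3.2 | 33.5% vs 62.0% | 28.5 | 63.2% | 65.9% |
| 10% | 6.4 | 37.0% vs 64.0% | 27.0 | 58.2% | 63.5% |
| 15% | 9.6 | 40.5% vs 66.0% | 25.5 | 53.5% | 60.9% |
| 20% | 12.8 | 44.0% vs 68.0% | 24.0 | 48.9% | 58.2% |

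Restricting the analysis restores the 30-point difference. Despite the smaller number of patients, it also gives more power than the diluted analysis at every p above zero in the table.

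**4. Is the restricted comparison still randomised?** Yes. The central M0 sample is taken at the inclusion visit (section 8.5), and rituximab in the personalised arm starts 5 to 14 days after randomisation (section 8.4). The subset is therefore defined by a value obtained before any study rituximab.

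**The case against.** The strongest reply is that central confirmation already does the work. A patient who is not confirmed is excluded and replaced, and ELISA in RU/ml is the only method that section 3 names for the trial's own titre. In the personalised arm the M0 pathways are restricted anti-CysR or anti-CTLD1/7 activity; an antibody-negative state is provided for only from M6. A natural reading is that everyone is ELISA-positive at M0, in which case p is zero. This is a fair reading and may be what is intended. But it is an inference: section 6.2 does not say it, and section 6.1 accepts IFA as evidence of activity in its own right.

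A second reply is that the effect is limited. Dilution is conservative for the comparison, objective 8 compares the titre itself between arms, and entrants have active disease, in which section 1.1 says titres usually rise. All of that stands, and it keeps the point modest. It does not make the stated rule classify such a patient correctly. Nor is this a detail that can simply be left to a statistical analysis plan, because the protocol itself fixes the definition.

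Three stronger readings are not supported:

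- A reader might infer that patients enter on IFA alone and are remissions from the outset. Central confirmation is required, and M0 is not counted.
- A reader might infer that objective 10 would find baseline titre to be a predictor by construction. Baseline PLA2R1 antibody titre is not among the risk factors listed under criterion 10. Only the misclassification of the outcome remains.
- A reader might price a chance excess of two such patients in an arm of 32 at the full 2/32. That assumes neither would have remitted anyway, and a chance imbalance is not a systematic bias.

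**Conclusion.** The point holds in a conditional form. Criterion 3, as written, counts a level rather than a depletion, and nothing in the protocol guarantees that every patient starts at or above that level. If some do not, and remain below it, both arms' rates are inflated and the difference shrinks by (1-p): from 30 points to 28.5 at p = 5% and to 25.5 at p = 15%. Those shares and the 30-point difference are assumptions. The true p cannot be derived from the protocol, and it is zero if central confirmation means ELISA at 14 RU/ml or above. Equal p in the two arms is what randomisation gives on average.

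The effect is confined to objective 3 and the immunological part of objective 10. Clinical remission at M12, the primary endpoint, does not use the titre. This is a cheap improvement to a secondary endpoint, and no threat to the trial's main conclusion.

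**What to change.** - **Section 3, criterion 3:** define immunological remission as a central ELISA titre below 14 RU/ml in a patient whose central ELISA titre at M0 was at least 14 RU/ml.
- **Section 12.3.2 and objective 10:** analyse objective 3 and the immunological part of objective 10 in that set, by randomised arm for objective 3. List patients below 14 RU/ml at M0 separately, by arm, as not evaluable for this criterion. They stay in every other analysis.
- **Section 6.2:** state the assay and cut-off for central confirmation. If that is already ELISA at 14 RU/ml or above, one sentence says so and the set is everyone confirmed.

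The cost is wording. The central M0 sample is already collected in both arms, so no new measurement is needed. The one downside is that a few patients may leave these secondary analyses, which then depart from the full intention-to-treat set. Because the set is fixed by a value obtained before any study rituximab, the comparison in objective 3 remains randomised.
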